## Abstract

**Importance:**

Exercise is considered a cornerstone of Metabolic dysfunction–associated steatotic liver disease (MASLD) management, but the independent role of exercise intensity in hepatic fat reduction has not been fully elucidated in clinical practice. The primary objective in this study is to evaluate the difference in exercise-induced reduction of hepatic fat content (HFC) between energy-matched high-intensity interval training (HIIT) and moderate-intensity continuous training (MICT). Furthermore, this study aims to investigate whether high-intensity exercise with lower exercise volume can yield comparable HFC reductions to moderate-intensity continuous training.

**Methods:**

This single-center, three-arm, open-label randomized controlled trial will recruit 105 adults aged 18–45 years with MASLD. Participants will be randomized in a 1:1:1 ratio to HIIT, MICT, or a low-volume HIIT (LHIIT). The sample size of 35 participants per group was calculated to provide 90% power to detect a significant difference in HFC reduction between the HIIT and MICT groups (two-sided α = 0.05, accounting for 20% dropout). The supervised exercise training will be conducted at a community fitness center for 12 weeks. The primary outcome is the absolute change in HFC, measured by magnetic resonance imaging–proton density fat fraction. Secondary outcomes include anthropometric parameters, abdominal adipose tissue, body composition, cardiometabolic biomarkers, and cardiorespiratory fitness. The analysis of the primary and secondary outcomes will be conducted according to the intention-to-treat principle.

**Discussion:**

This trial rigorously evaluates the independent effect of exercise intensity on HFC under energy-matched conditions, while simultaneously exploring the therapeutic efficiency of low-volume interventions. The findings of this study are expected to provide a theoretical and practical basis for precise exercise prescriptions for the MASLD population. The results will be disseminated through a peer-reviewed journal.

**Clinical Trial Registration:**

https://www.chictr.org.cn/showprojEN.html?proj=279678, identifier ChiCTR2500107821.

## Introduction

1

Obesity is a major driver of metabolic disorders, with its progression significantly increasing the prevalence of complications. In China, metabolic-associated steatotic liver disease (MASLD) is the most common obesity-related complication and the leading chronic liver disease (1). It is estimated that the number of people with MASLD in China will reach 314 million by 2030 (2). Excessive visceral fat, particularly hepatic fat accumulation, serves as a stronger predictor for cardiovascular diseases (CVDs) than obesity alone (3). Moreover, hepatic fat content (HFC) is closely associated with the onset of type 2 diabetes (T2DM) (4). Therefore, early intervention for individuals with MASLD is essential to delay disease progression and reduce the risk of T2DM and CVDs.

Currently, lifestyle modifications, including dietary changes and increased physical activity, are the primary treatment approaches for MASLD (5). Among these, exercise has shown a dose-response relationship with reductions in HFC (6), and importantly, its effects may be independent of body weight changes (7). Specifically, high-intensity interval training(HIIT) demonstrates a similar reduction in HFC compared to moderate-intensity continuous training (8). Current guidelines propose that exercise volume, rather than intensity, is the principal determinant of HFC reduction (9). Conversely, Winn et al. reported that isoenergetic HIIT resulted in an 84% greater HFC reduction than MICT (10). However, this finding lacked statistical significance, which was attributed to the insufficient sample size (10). Moreover, Taylor et al. observed a non-significant trend (p=0.077) favoring HIIT over moderate-intensity continuous training (MICT) for hepatic fat reduction following a 3-month intervention (3 times/week) in cardiac rehabilitation individuals (11). Consequently, it remains uncertain whether, for a given exercise volume, higher intensity exercise offers an independent advantage over lower intensity exercise for mitigating liver fat accumulation. AMP-activated protein kinase (AMPK) serves as a pivotal signal modulator of exercise adaptation, functioning as an ‘energy switch’ that regulates cellular energy homeostasis (12). Emerging research indicates that AMPK and its downstream signaling pathways are closely linked to the mitigation of hepatic fat accumulation, positioning AMPK agonists as potential therapeutic targets for MASLD (13). As a cellular energy sensor, AMPK is primarily activated by elevations in ADP concentration, a metabolic perturbation that is significantly amplified by higher exercise intensities (14). From this perspective, short-duration high-intensity exercise holds significant therapeutic potential for reducing HFC in the MASLD population. Additionally, higher exercise intensity can achieve faster consumption of muscle glycogen (15), which helps to improve the competitive inhibition of substrate oxidation under the condition of high substrate flux after meals (13, 16, 17), thereby reducing the accumulation of fat content in the liver. We hypothesize that exercise-induced muscle glycogen depletion may be a regulatory pathway for exercise to reduce HFC, and thus higher exercise intensity may be more efficient in reducing HFC.

Therefore, the present study aims to clarify the independent role of exercise intensity in hepatic fat reduction among individuals with MASLD. To achieve this, we will primarily compare HIIT with MICT under matched energy expenditure. In addition, a low-volume HIIT group with approximately half the prescribed energy expenditure has been included to examine whether high-intensity exercise yields comparable efficiency in reducing HFC with high-volume moderate intensity exercise. We hypothesize that under energy-matched conditions, HIIT will elicit a significantly greater reduction in HFC compared to MICT, while low-volume HIIT will induce comparable reductions to MICT despite a lower total energy expenditure. This design will enable a comprehensive evaluation of exercise intensity as a critical determinant of exercise-induced changes in HFC.

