### Research design

2.1

This trial is a single-center, three-arm, open-label randomized controlled study (**Figure 1**). As a superiority trial, a non-exercise control group will not be included, given that numerous studies have already demonstrated the significant efficacy of aerobic training for decreasing HFC in individuals with MASLD. A total of 105 eligible participants aged 18–45 years will be randomized in a 1:1:1 ratio to the high-intensity interval training (HIIT) group, moderate-intensity continuous training (MICT) group, or low-volume HIIT (LHIIT) group. The intervention will last 12 weeks. The HIIT and MICT groups will perform exercise sessions aiming for approximately 400 kcal per session (~1200 kcal/week), while the LHIIT group will perform shorter sessions of approximately 200 kcal per session. To minimize confounding factors, all participants will receive standardized dietary guidance to maintain a stable caloric intake consistent with their baseline habits during the intervention period. All exercise sessions will be supervised by certified exercise trainers to ensure adherence, safety, and fidelity to the protocol. Due to the nature of the interventions, participants and trainers cannot be blinded; however, outcome assessors, imaging analysts, and statisticians will remain blinded to allocation. The primary outcome is the change in HFC, quantified by magnetic resonance imaging–proton density fat fraction (MRI-PDFF), with the primary comparison set between HIIT and MICT. Analyses involving the LHIIT group are considered exploratory and will be interpreted as hypothesis-generating. This trial protocol has been reviewed and approved by the Ethics Committee of the First Affiliated Hospital of Naval Medical University (CHEC2025-253) and registered on the Chinese Clinical Trial Registry (ChiCTR2500107821). Any modifications to the protocol will be fully documented and described in detail in subsequent publications.

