### Statistical analysis plan

2.7

Baseline characteristics and study outcomes will be summarized using descriptive statistics. The normality of continuous variables will be assessed using the Shapiro-Wilk test and visual inspection of histograms and Q-Q plots. Continuous variables with a normal distribution will be presented as means ± standard deviations (SD), while non-normally distributed variables will be reported as medians and interquartile ranges (IQR). Treatment effects will be reported as the estimated mean difference (MD) between groups with 95% confidence intervals (CIs) to provide a clear estimation of the effect size. Categorical variables will be expressed as frequencies and percentages (n, %). Baseline differences between groups will be assessed using one-way ANOVA or Kruskal-Wallis tests for continuous variables, and Chi-square tests or Fisher’s exact tests for categorical variables.

The analysis will be conducted according to the Intention-to-Treat (ITT) principle, including all randomized participants (N = 105) for both primary and secondary endpoints. To address missing data arising from participant withdrawal, Multiple Imputation by Chained Equations (MICE) (m=20 imputed datasets) will be performed prior to the primary analysis. Treatment effects will be evaluated using analysis of covariance (ANCOVA). The post-intervention measurements will be included as the dependent variable. Fixed effects will include group (HIIT, MICT, LHIIT), and the baseline measurements will be included as a covariate. The results from the imputed datasets will be pooled using Rubin’s rules. Tukey’s Honestly Significant Difference test will be used for *post-hoc* pairwise comparisons. Furthermore, sensitivity analyses for primary outcome will be conducted to assess the robustness of the results. These will include: (1) a Per-Protocol analysis; (2) an analysis excluding participants with >5% body weight change; and (3) an analysis including percentage body weight change as a covariate in the primary ANCOVA model. All statistical analyses will be performed using R software (version 4.5.1). A two-sided p-value< 0.05 will be considered statistically significant.

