The distinct advantage of high-intensity intervention lies in its potential to achieve HFC reductions comparable to MICT with reduced time and energy expenditure, or potentially superior reductions when energy is matched. This provides diverse, efficient intervention options for the heterogeneous MASLD population. However, the optimal physiological boundaries for intensity and volume in this population remain undefined. It cannot be assumed *a priori* that the high-volume HIIT (400 kcal) will inherently outperform low-volume LHIIT (200 kcal). Individuals with metabolic dysfunction may exhibit impaired metabolic flexibility or maladaptation to high physiological loads (32, 33). Therefore, determining the effective physiological threshold and establishing safe dosage boundaries based on individual metabolic characteristics represent critical questions worthy of further investigation.

Collectively, the results of this study facilitate a flexible approach to exercise prescription for MASLD, tailoring the regimen to the time availability and fitness level of MASLD population. We propose that low-volume HIIT is an optimal strategy for time-poor individuals, while high-volume HIIT serves those prioritizing maximal fat reduction. For patients unable to tolerate high intensities, volume-compensated moderate-intensity exercise offers a dependable alternative for managing HFC.

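### The aim and hypothesis that low-volume HIIT is 'comparable' to MICT do not match the planned analysis, which has a difference test and confidence intervals but no margin

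*Protocol article*

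**What the plan says.** **The question.** The Abstract of the protocol article (Importance) gives as a further aim to investigate "whether high-intensity exercise with lower exercise volume can yield comparable HFC reductions to moderate-intensity continuous training". The Introduction turns this into a hypothesis: "while low-volume HIIT will induce comparable reductions to MICT despite a lower total energy expenditure". Neither place says how close the two arms must be to count as comparable, and no later section does.

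**The framework.** Section 2.1 describes the study "As a superiority trial, a non-exercise control group will not be included", "with the primary comparison set between HIIT and MICT". It adds: "Analyses involving the LHIIT group are considered exploratory and will be interpreted as hypothesis-generating". Section 2.6 sizes the trial for HIIT versus MICT alone.

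**The analysis.** Section 2.7 fits an ANCOVA with three groups and reports mean differences with 95% confidence intervals. For the pairwise contrasts, Tukey's "Honestly Significant Difference test will be used for" post-hoc use, and "A two-sided p-value< 0.05 will be considered statistically significant". No equivalence or non-inferiority margin is given.

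**The anticipated message.** Section 3 states: "We propose that low-volume HIIT is an optimal strategy for time-poor individuals".

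**The concern.** A hypothesis of comparability needs a criterion that the data can meet. A difference test offers none: when it fails to reject, the cause may be similar arms or too little information. A confidence interval could settle the matter, but only against a stated limit for how much of the MICT benefit may be lost. The Tukey adjustment widens the threshold, which makes a non-significant LHIIT versus MICT result more likely still.

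At stake is what the trial may conclude about its third arm. Without a criterion, whether LHIIT proved comparable is left to judgement after the results are known, and section 3 already shows which conclusion is expected.

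**Working it through.** **Inputs from section 2.6:** anticipated reductions 1.7 (SD 1.1) for HIIT and 0.9 (SD 0.7) for MICT, in percentage points of MRI-PDFF; pooled SD 0.92; two-sided α 0.05; power 90%; 28 evaluable and 35 randomised per arm.

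**Assumptions, because the article gives no figure:** SD 0.92 also holds for LHIIT; baseline adjustment brings no gain in precision; losses and margins are illustrative and shown over a range.

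**1. The plan's own figure.**
- Pooled SD = √[(1.1² + 0.7²)/2] = 0.92.
- n = 2 × 0.92² × (1.960 + 1.282)² / 0.8² = 27.8, rounded up to 28.
- 28 / 0.8 = 35.

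The stated sample size is reproduced. It concerns HIIT versus MICT only.

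**2. Precision for LHIIT versus MICT at 28 per arm.**
- SE = 0.92 × √(2/28) = 0.246.
- Residual degrees of freedom = 3 × 28 − 4 = 80.
- Unadjusted 95% half-width = 1.990 × 0.246 = 0.49, which is 54% of the anticipated 0.9-point MICT reduction.
- Tukey half-width = 2.388 × 0.246 = 0.59, which is 65% of it.

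**3. Chance of a non-significant result when LHIIT is truly worse** (noncentral t with noncentrality = loss / SE; for a loss of 0.45, 0.45 / 0.246 = 1.83).

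| True loss (points) | 28 per arm: Tukey / unadjusted | 35 per arm: Tukey / unadjusted |
|---|---|---|
| 0.30 | 87% / 77% | 84% / 73% |
| 0.45 (half of 0.9) | 71% / 56% | 63% / 47% |
| 0.60 | 48% / 33% | 36% / 23% |

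The 35-per-arm columns use SE = 0.92 × √(2/35) = 0.220 and a Tukey critical value of 2.379.

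**4. Chance of showing non-inferiority when the arms are truly equal.** Here the bound of the unadjusted two-sided 95% interval on the side of LHIIT's loss must stay within the margin, at 28 per arm:

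| Margin (points) | Share of the 0.9-point MICT effect | Power |
|---|---|---|
| 0.30 | 33% | about 23% |
| 0.45 | 50% | 44% |
| 0.60 | 67% | 67% |
| 0.80 | 89% | about 90% |

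The planned size therefore reaches about 90% only with a margin that gives away most of the MICT effect. If the whole interval had to lie within ±0.45, power would be about 1%, because the half-width of 0.49 already exceeds the margin.

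**The case against.** The strongest defence is that the protocol already ranks its questions. HIIT versus MICT is primary and is the only comparison that is sized; LHIIT is declared exploratory; and section 2.7 commits to mean differences with 95% intervals, so the result will be shown as an estimate and not only as a p-value. All of this stands and lowers the severity. It does not supply a criterion for comparability, which remains an aim and a hypothesis.

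A reader might infer that the authors will treat p>0.05 as comparability. The article states no such rule, and section 2.1 says that these analyses will be read as hypothesis-generating. The supported point is narrower: a non-significant result could not carry that conclusion.

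The 0.45-point loss is not a protocol figure, and the cited evidence points the other way. Section 3 describes the study behind the sample size as one of low-volume HIIT, with an 89% larger reduction than MICT ((1.7 − 0.9) / 0.9 = 89%), although not significantly so. If LHIIT were truly better, non-inferiority would be easier to show: at a margin of 0.45 and 28 per arm, power is about 74% for a true advantage of 0.2 points and about 92% for 0.4. This stands, and the 44% applies only at a true difference of zero. It is an argument for writing the criterion down, not for leaving it out.

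Section 3 is also more guarded than its one sentence on LHIIT suggests: it calls the benefit potential and the optimal limits of intensity and volume undefined. The sentence is discussion prose and not a decision rule, but as worded it does not wait for the results.

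A reader might also hold the missing non-exercise arm against this comparison. Section 2.1 gives a reason for that choice, and it is not part of this point.

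**Conclusion.** The point holds as a mismatch between a stated aim and hypothesis and the stated analysis. It is a matter that should be corrected, not one that threatens the trial: the primary comparison and its sample size are untouched.

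Its size, under the assumptions above, is that a loss of half the anticipated MICT effect would go undetected in about 71% of trials with Tukey at 28 per arm, and in 63% with all 35 measured. A useful gain in precision from baseline adjustment would lower these figures, but the article gives no correlation from which to compute it. The logical point, that non-significance is not evidence of similarity, depends on none of these numbers. A full protocol or separate analysis plan, not shown, might contain a margin; the article's own analysis section does not.

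**What to change.** Choose one of two changes before unblinding.

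**(a) Keep the claim and give it a criterion.** Prespecify and justify a non-inferiority margin for LHIIT versus MICT in section 2.7. Allow the word 'comparable' only if the bound of the unadjusted two-sided 95% confidence interval on the side of LHIIT's loss stays within that margin. Say explicitly that this is a one-sided reading. In section 2.6, state the power at a true difference of zero for the chosen margin, and note that it is higher if LHIIT is truly better.

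**(b) Change the claim to estimation.** Reword the Abstract aim and the Introduction hypothesis as estimating the LHIIT–MICT difference with its 95% confidence interval. State in section 2.7 that p>0.05 will not be taken as comparability. Remove the LHIIT statement in section 3 or make it conditional on the results.

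Option (b) fits the exploratory label and the intervals already planned. Either option costs wording only, with no added participants or measurements. The downside is that the comparability claim may not be attainable: under (a) power is low for any margin well below the full MICT effect unless LHIIT is truly better, and under (b) the claim is given up.

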## Methods

2

### Research design

2.1

This trial is a single-center, three-arm, open-label randomized controlled study (**Figure 1**). As a superiority trial, a non-exercise control group will not be included, given that numerous studies have already demonstrated the significant efficacy of aerobic training for decreasing HFC in individuals with MASLD. A total of 105 eligible participants aged 18–45 years will be randomized in a 1:1:1 ratio to the high-intensity interval training (HIIT) group, moderate-intensity continuous training (MICT) group, or low-volume HIIT (LHIIT) group. The intervention will last 12 weeks. The HIIT and MICT groups will perform exercise sessions aiming for approximately 400 kcal per session (~1200 kcal/week), while the LHIIT group will perform shorter sessions of approximately 200 kcal per session. To minimize confounding factors, all participants will receive standardized dietary guidance to maintain a stable caloric intake consistent with their baseline habits during the intervention period. All exercise sessions will be supervised by certified exercise trainers to ensure adherence, safety, and fidelity to the protocol. Due to the nature of the interventions, participants and trainers cannot be blinded; however, outcome assessors, imaging analysts, and statisticians will remain blinded to allocation. The primary outcome is the change in HFC, quantified by magnetic resonance imaging–proton density fat fraction (MRI-PDFF), with the primary comparison set between HIIT and MICT. Analyses involving the LHIIT group are considered exploratory and will be interpreted as hypothesis-generating. This trial protocol has been reviewed and approved by the Ethics Committee of the First Affiliated Hospital of Naval Medical University (CHEC2025-253) and registered on the Chinese Clinical Trial Registry (ChiCTR2500107821). Any modifications to the protocol will be fully documented and described in detail in subsequent publications.

**Figure 1 f1:**
[figure not shown]
Flow paradigm.

### Subjects

2.2

This study aims to recruit a total of 105 participants at the First Affiliated Hospital of Naval Medical University, with recruitment scheduled from January 2026 to January 2028. **Table 1** summarizes the detailed inclusion and exclusion criteria for participant selection. Recruitment will be facilitated through hepatology and weight management outpatient clinics at the hospital. Additionally, informational flyers will be distributed in community hospitals and health examination centers within a 5-kilometer radius of the main hospital to expand outreach efforts. Potential participants will be initially screened through review of their electronic medical records by study investigators to assess eligibility. Eligible individuals will then be invited to provide written informed consent by research staff, followed by completion of baseline assessments within four weeks of enrollment.

**Table 1 T1:** Inclusion and exclusion criteria.

Inclusion criteria
- Age between 18 and 45 years, with no restrictions on gender
- Meets the diagnostic for MASLD
- Medication type and dosage have remained stable over the past three months
- No regular exercise routine(3 sessions/week, 30 minutes/session)
Exclusion criteria
- Weight change exceeding 5% in the past three months
- Inability to maintain blood glucose and blood pressure within normal ranges despite standard treatment
- Inability to participate in exercise testing and training due to any condition
- Women who are pregnant, planning to conceive, or in the periconceptional period
- Currently undergoing any form of hormone therapy.

**Table 1** outlines the inclusion and exclusion criteria. Individuals meeting the following criteria will be recruited: 1) An age range of 18 to 45 years, with no gender restrictions; 2) Fulfilling the diagnostic criteria for MASLD, as defined by Eslam et al. (18); 3) A stable medication type and dosage over the past three months; 4) No regular exercise routine (defined as participating in physical activity fewer than three times per week, with each session lasting less than 30 minutes, over the past three months). Individuals presenting with any of the following conditions will be excluded: 1) Weight change exceeding 5% in the past three months; 2) Inability to maintain blood glucose and blood pressure within normal ranges despite standard treatment; 3) Inability to participate in exercise testing and training due to any condition (e.g., severe cardiovascular, pulmonary, or renal diseases, musculoskeletal injuries, etc.); 4) Women who are pregnant, planning to conceive, or in the periconceptional period; 5) Currently undergoing any form of hormone therapy.

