### Randomization

2.3

A stratified block randomization method will be employed in this study. Participants will be randomly assigned to the following three groups: MICT group (n=35), HIIT group (n=35), and LHIIT group (n=35). Stratification is based on sex (male and female) and age. Stratification will be based on participant gender (Male, Female) and age group (18–30 years and 31–45 years), resulting in four distinct strata. Within each stratum, a computer-generated randomization sequence will be created using permuted blocks of size 6. The randomization list was generated prior to study commencement using R 4.5.1. To ensure allocation concealment, sequentially numbered, opaque, sealed envelopes will be prepared in advance based on the stratified randomization list. Following eligibility confirmation and informed consent, the research coordinator allocated the participant to the treatment group indicated in the next available envelope within the appropriate stratum.

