#### Primary outcomes

2.4.1

The primary outcome is the absolute change in HFC, quantified as MRI-PDFF, from baseline to 12 weeks. All MRI-PDFF measurements will be acquired using a standardized multi-echo gradient-echo sequence on the same 3.0T scanner (Magnetom Prisma, Siemens Healthineers, Erlangen, Germany), using an 18-channel body and a 32-channel spine phased-array coil, conducted by a single professional technician who is blinded to group allocation. A multi-echo 3D spoiled gradient-echo sequence (Volumetric Interpolated Breath-hold Examination-Based, VIBE) integrated within the Siemens LiverLab sequence will be performed under a single end-expiratory breath-hold. Typical acquisition parameters included: repetition time (TR)< 12 ms, six asymmetric echo times (TEs, e.g., first TE ~1.2ms, echo spacing ~1.2ms), flip angle ~3-6°, axial orientation, field of view covering the entire liver, and parallel imaging. PDFF maps will be automatically generated by LiverLab, which employs a multi-peak fat spectral model and corrects for T2-weight decay. The liver will be segmented using an artificial intelligence algorithm embedded in the assessment program. Segmentations with a goodness-of-fit exceeding 95% will be accepted after reviewing the images and reports.

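### Eligibility does not require that a participant can be scanned, and randomisation is scheduled before the first MRI, so people who cannot supply the primary outcome can be randomised

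*Protocol article*

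**What the plan says.** Section 2.2 says that Table 1 "summarizes the detailed inclusion and exclusion criteria for participant selection". Table 1 and the text each give four inclusion and five exclusion criteria. One exclusion deals with ability to complete study procedures: "Inability to participate in exercise testing and training due to any condition". It names exercise testing and training, and its examples are conditions that limit exercise. No criterion mentions MRI.

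Section 2.4.1 defines the endpoint: "The primary outcome is the absolute change in HFC, quantified as MRI-PDFF, from baseline to 12 weeks". All measurements are made "on the same 3.0T scanner", and the sequence "will be performed under a single end-expiratory breath-hold". Two successful scans per person are needed.

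Table 2 ticks randomisation in the screening column only. It ticks MRI-PDFF at week 0 and week 12 only. Section 2.3 makes allocation depend on two things: "Following eligibility confirmation and informed consent, the research coordinator allocated the participant to the treatment group". A baseline scan is not one of them.

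Section 2.7 analyses by intention to treat, "including all randomized participants (N = 105) for both primary and secondary endpoints". It enters the baseline measurement as the ANCOVA covariate and fills gaps with 20 chained-equation imputations. The reason it gives for missing data is withdrawal.

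**The concern.** The plan checks before allocation that a participant can do the intervention, but does not require a check that the participant can provide the primary measurement. An implant, claustrophobia or difficulty holding the breath at end-expiration need not prevent treadmill exercise, so the exercise clause does not reach these people.

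The scheduled order turns a missing line into a practical problem. If the scan came first, an unscannable person would simply be a screen failure. With allocation first, that person is already randomised when the scan fails, and the analysis rule keeps them in. Their baseline and 12-week PDFF are then both imputed. They add essentially nothing on the HIIT–MICT difference in liver fat, apart from whatever other variables in the imputation model can predict. This loss also has a different cause from the withdrawal that section 2.7 cites and from the dropout for which section 2.6 inflates the sample.

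**Working it through.** **1. Inputs from section 2.6.** Anticipated changes −1.7 (SD 1.1) for HIIT and −0.9 (SD 0.7) for MICT, so the difference is 0.8 points. Pooled SD 0.92, two-sided α 0.05, power 90%, 28 per group, 20% dropout, 35 per group, 105 in total.

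**2. Reproducing the plan's figures.**
- Pooled SD: √((1.1² + 0.7²)/2) = 0.922.
- Normal approximation: n = 2 × (1.960 + 1.282)² × (0.92/0.8)² = 27.8, so 28 per group.
- Dropout: 28/0.8 = 35, and 3 × 35 = 105.

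The plan's numbers reproduce. Since 35 × 0.8 is exactly 28, nothing is left over once the full dropout allowance is used.

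**3. Sequence in the text.**

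| Step | Source | Is ability to be scanned required? |
|---|---|---|
| Eligibility | Table 1, section 2.2 | No |
| Envelope opened | Section 2.3; Table 2, screening | No |
| First MRI-PDFF | Table 2, week 0 | First test of it |
| Analysis set | Section 2.7 | All randomised kept |

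**4. Illustrative cost.** Let p be the share of randomised people who cannot be scanned. The document gives no value, so p is assumed: 2–5% as the working range, with 10% as a high case. If these people come on top of the full 20% dropout, the evaluable number per arm is 35 × 0.8 × (1 − p). Power is for a two-sample comparison with difference 0.8 and SD 0.92.

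| p | Unscannable of 105 | Evaluable per arm | Power, t-test | Power, normal approx. |
|---|---|---|---|---|
| 0% | 0 | 28.0 | 89.2% | 90.2% |
| 2% | 2.1 | 27.4 | 88.5% | 89.6% |
| 5% | 5.2 | 26.6 | 87.5% | 88.7% |
| 10% | 10.5 | 25.2 | 85.7% | 87.0% |

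The loss is about 0.6 points at 2%, about 1.5 to 1.6 at 5%, and about 3.2 to 3.5 at 10%. The start at 89.2% in the t-test column reflects only the difference between the t-based and normal formulas at n = 28 and has nothing to do with MRI.

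If the 20% allowance is instead read as covering people who cannot be scanned, the evaluable number stays at 28 and the power loss is nil.

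**The case against.** The strongest reply is that a journal article condenses the protocol, and that MRI contraindications and the imaging unit's safety form are routine details left to the full document. That would answer a complaint resting on silence alone. This point also rests on what the article states: a criteria list described as detailed, given in both table and text, and a schedule that puts randomisation before the first scan. A fuller protocol or Figure 1, which is not shown, might contain an MRI check, and that uncertainty remains.

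A second reply is that Table 2 is a coarse grid; it also ticks adherence at screening, before any training. Section 2.9 has physicians carry out baseline health assessments to confirm eligibility, so some baseline work precedes allocation. But that check concerns suitability for exercise testing and the interventions. The four-week window for baseline assessments in section 2.2 does not place the scan before the envelope either.

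A third reply largely stands. Records are reviewed before consent and medical history is taken at screening, so staff would often see a known implant in time, although no written rule excludes that person. Claustrophobia or a failed breath-hold is less likely to be on record.

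The criticism of the size also stands. The rate is assumed, stacking it on the whole dropout allowance is a choice, and the planned analysis is ANCOVA. Its residual variance is no larger than that of the change score, so actual power is probably higher than the t-test figures.

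A reader might infer that the gap biases the HIIT–MICT comparison or leaves the trial underpowered. The documents support neither. Being unscannable is a pre-allocation characteristic with no reason to differ by arm, and the sample size reproduces with only a small loss under the assumed rates. Nor does the text show that no MRI safety screening takes place; it shows only that none is required before allocation.

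**Conclusion.** The point holds as a minor design gap. The listed criteria do not require ability to undergo the scan that provides the primary outcome and its covariate, and the stated schedule allocates before that scan. Someone who cannot be scanned can therefore be randomised and must be analysed with both PDFF values imputed.

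The consequence is avoidable missing primary data and a slight loss of precision: roughly 1–2 points of power if 2–5% of participants (about 2 to 5 of 105) cannot be scanned. That figure assumes a rate the document does not give, losses on top of the full 20% dropout, and a t-test in place of the planned ANCOVA, so it indicates scale only. The figures of 28, 35 and 105 are unaffected.

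**What to change.** Make two changes.

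1. In Table 1 and section 2.2, add an exclusion for contraindication to, or inability to complete, the 3.0T MRI examination including the breath-hold.
2. In Table 2 and section 2.3, move randomisation after the baseline MRI-PDFF, so that the envelope is opened only after eligibility, consent and a successfully acquired baseline scan. The segmentation acceptance rule in section 2.4.1 can help define success.

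At minimum, complete the MRI safety form at screening, before allocation. This alone is weaker, because a paper form cannot show that someone tolerates the scanner or completes the breath-hold.

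The scan is already planned, so no procedure is added. The cost is a few more screen failures, some baseline scans on people who are then not randomised, and a slightly narrower population. At the assumed 2–5%, reaching 105 randomised would take about 105/0.98 = 107 to 105/0.95 = 111 people brought to the baseline scan, roughly 2 to 6 more than now.
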